## Abstract

**Background:**

Diabetic foot ulcers are a common and severe complication of diabetes mellitus. Standard treatment includes debridement, offloading, management of infection and revascularisation where appropriate, although healing times may be long. The LeucoPatch® device is used to generate an autologous platelet-rich fibrin and leucocyte wound dressing produced from the patient’s own venous blood by centrifugation, but without the addition of any reagents. The final product comprises a thin, circular patch composed predominantly of fibrin together with living platelets and leucocytes. Promising results have been obtained in non-controlled studies this system, but this now needs to be tested in a randomised controlled trial (RCT). If confirmed, the LeucoPatch® may become an important new tool in the armamentarium in the management of diabetic foot ulcers which are hard-to-heal.

**Methods:**

People with diabetes and hard-to-heal ulcers of the foot will receive either pre-specified good standard care or good standard care supplemented by the application of the LeucoPatch® device.

The primary outcome will be the percentage of ulcers healed within 20 weeks. Healing will be defined as complete epithelialisation without discharge that is maintained for 4 weeks and is confirmed by an observer blind to randomisation group.

**Discussion:**

Ulcers of the foot are a major source of morbidity to patients with diabetes and costs to health care economies. The study population is designed to be as inclusive as possible with the aim of maximising the external validity of any findings. The primary outcome measure is healing within 20 weeks of randomisation and the trial also includes a number of secondary outcome measures. Among these are rate of change in ulcer area as a predictor of the likelihood of eventual healing, minor and major amputation of the target limb, the incidence of infection and quality of life.

**Trial registration:**

International Standard Randomised Controlled Trial, ISRCTN27665670. Registered on 5 July 2013.

## Background

### Diabetic foot ulcers

Diabetic foot ulcers (DFU), a common and severe complication of diabetes mellitus, are currently the most common chronic type of wound in Western industrialised countries [1]. Despite improved outcomes following modern standard treatment, DFUs are still the predominant reason for non-traumatic leg amputation in most Western countries, amputation rates in patients with diabetes being described as much as 15-fold higher than those in non-diabetic populations [2].

Diabetic foot ulceration is the consequence of neuropathy and micro- and macrovascular disease [3]. The syndrome is frequently worsened by infection [4].

As all aspects of this multifactorial aetiology must be taken into account, modern standard treatment includes regular debridement, off-loading, treatment of infection, revascularisation when appropriate, optimising metabolic control and the treatment of any concomitant diseases, as well as education about foot care and the provision of appropriate footwear [5, 6].

If these treatment strategies are properly applied the majority of chronic non-healing ulcers will heal, although healing times may be prolonged [1].

The presence of a DFU is also associated with significant reduction in health-related quality of life (HRQoL); ulcer healing is associated with improved HRQoL [7, 8].

### Growth factors and healing

Growth factors are involved throughout the healing process [9–11]. At the cellular level growth factors mediate macrophage migration, neovascularisation, collagen synthesis, fibroblast proliferation as well as epithelialisation [12–15].

Animal, as well as in-vitro studies, have shown positive effects of platelet-derived growth factors on ulcer healing [16, 17]. Platelets contain a range of potent growth factors. These consist, among others, of platelet-derived growth factor (PDGF), transforming growth factor-β (TGF-β), epidermal growth factor (EGF) and vascular endothelial growth factor (VEGF), which together exhibit different chemotactic, mitogenic and proliferative properties.

The first clinical study evaluating the effect of platelet-derived growth factors on ulcer healing was performed by Knighton et al. in 1986 [18]. In this small, prospective, randomised, blinded, placebo-controlled, cross-over study the effect of a platelet-derived, wound-healing formula (PDWHF) was evaluated. The frequency of complete epithelialisation of ulcers was significantly higher in PDWHF-treated patients when compared to controls (87% versus 15%), and, after cross-over, complete epithelialisation was achieved in the control group after 7.1 weeks [18]. In a case-series of 24 patients, Crovetti et al. achieved sustained ulcer healing in eight patients with chronic cutaneous ulcers, and ulcer area reduction in another seven cases, after topical treatment with a platelet gel [19].

In a retrospective cohort study, Margolis et al. estimated the effectiveness of platelet releasate in the treatment of diabetic neuropathic foot ulcers using the Curative Health Services database including 120,000 patients with chronic wounds. The analysis suggested that treatment with platelet releasate was more effective than standard therapy, with the most pronounced beneficial effect being seen in more serious ulcers [20]. However, Stacey et al. found no effect on the healing of chronic venous leg ulcers using lysed platelets in a randomised, double-blind, placebo-controlled study [21]. Neither could Senet et al. show any beneficial effect on healing of chronic venous leg ulcers [22].

Since the study by Knighton et al., many methods for producing platelet releasate, platelet gel and fibrin-platelet suspensions have been developed. They are all quite complex and all require the addition of different reagents, and thus cannot by definition be characterised as purely autologous products. The concentration and activation of platelets in these products varies and, despite promising early results, the need for confirmation in large, good-quality randomised controlled trials (RCTs) remains [6].

### LeucoPatch®

The LeucoPatch® device is a CE-marked, single-use medical device used to generate an autologous platelet- and leucocyte-rich fibrin wound dressing named the LeucoPatch®. A LeucoPatch® is produced from the patient’s own venous blood by centrifugation, but without the addition of any reagents. The final product comprises a thin, circular patch composed predominantly of fibrin together with living platelets and leucocytes (Fig. 1). The number of LeucoPatches® applied can be adjusted to fit the individual wound. The yield of platelets is close to 100% and varies minimally from patient to patient. The content and release of growth factors of this product is equal to, or higher, than other reported preparations. The product differs from other autologous platelet products by containing a high concentration of fibrin as well as both platelets and leucocytes.

**Fig. 1 Fig1:**
[figure not shown]
A LeucoPatch® post centrifugation

In an initial pilot study, promising beneficial effects on ulcer healing after the application of the LeucoPatch® were seen [23]. Following this, in an open, clinical multicentre study including 41 patients with hard-to-heal DFUs (median ulcer duration of 40 weeks) an intention-to-treat (ITT) analysis showed that 12 (32%) healed within 12 weeks of once-weekly treatment and 22 (54%) healed within 20 weeks. No safety issues were raised in this trial [24]. This apparent beneficial effect now needs to be tested in a RCT. If confirmed, the LeucoPatch® may become an important new tool in the armamentarium for the management of DFUs which are hard-to-heal.

### Aims

This study will demonstrate whether the application of the LeucoPatch®, when used in addition to usual care in a multidisciplinary, diabetes foot clinic setting, is superior to usual care alone with regard to complete epithelialisation of hard-to-heal DFUs which are not infected at the time of randomisation. The Standard Protocol Items: Recommendations for Interventional Trials (SPIRIT) schedule is given in Fig. 2.

**Fig. 2 Fig2:**
[figure not shown]
Standard Protocol Items: Recommendations for Interventional Trials (SPIRIT) Checklist

## Methods

### Design

This is a multicentre, multinational, observer-blind, randomised controlled trial. Patients will be randomised 1:1 to the intervention or the usual-care arm.

### Study setting and participants

Participants will be recruited from specialist diabetes foot care clinics at sites in the UK, Denmark and Sweden.

Eligible participants will be people aged 18 years and over who have diabetes complicated by one or more foot ulcers. In addition, the following inclusion and exclusion criteria will apply:

### Inclusion criteria

Eligible ulcers will be below the level of the malleoli, excluding ulcers confined to the interdigital cleftEligible ulcers will be hard-to-heal, meaning that the cross-sectional area will decrease by less than 50% during a 4-week run-in periodThe cross-sectional area of the index ulcer will be ≥ 50 and ≤ 1000 mm^2^ at the end of the 4-week run-in periodAt randomisation, the index ulcer will be clinically non-infected according to the Infectious Diseases Society of America (IDSA) criteriaEither the Ankle-brachial Pressure Index (ABPI) in the affected limb will be between 0.50 and 1.40 or the dorsalis pedis pulse and/or the tibialis posterior pulse will be palpableGlycosylated haemoglobin (HbA_1c_) level ≤ 108 mmol/mol at screeningParticipants will have the capacity to understand study procedures, and will be able to provide written informed consent

### Exclusion criteria

Increase in cross-sectional area of the index ulcer by ≥ 25% during the 4-week run-in period, or is either smaller than 50 mm^2^ or larger than 1000 mm^2^ at the end of that timeClinical signs of infection of the index ulcer or reason to suspect that infection is present at randomisationRevascularisation procedure in the affected limb planned, or undertaken within the 4 weeks prior to screeningTreatment of foot ulcers with growth factors, stem cells or equivalent preparation within the 8 weeks prior to screeningThe need for continued use of negative-pressure wound therapyHaemoglobin concentration < 105 g/L or 6.5 mmol/L at screeningPresence of sickle-cell anaemia, haemophilia, thrombocytopenia (<100 × 10^9^/L) or other clinically significant blood dyscrasiaKnown potential infectivity of blood products, including known HIV and hepatitisDialysis or an estimated glomerular filtration rate (GFR) (based on cystatin C or serum creatinine) < 20 ml/min/1.73 m^2^
Current treatment with cytotoxic drugs or with systemically administered glucocorticoids or other immunosuppressants. Likely inability to comply with the need for weekly visits because of planned activityParticipation in another interventional clinical foot ulcer-healing trial within the 4 weeks prior to screeningPrior randomisation in this trialJudgement by the investigator that the patient does not have the capacity to understand the study procedures or to provide written informed consent

### Sample size

Previous non-controlled LeucoPatch® outcome data suggested a healing rate (intention-to-treat) of 54% during a 20-week follow-up period in a study population similar to this study population. Outcome data from a matched control group as well as from placebo/control groups in other diabetic foot studies with inclusion and exclusion criteria similar to these criteria indicate healing rates between 27 and 32% at 20 weeks’ follow-up, although some authors have reported healing rates below 10%.

A sample size for comparing two proportions with Fleiss continuity correction, based on alpha = 0.05 and beta = 80% and with an outcome rate in the control group of 30% and an improvement of 18 percentage points (i.e. to 48%) in the treatment group gives a sample size of 250 evaluable patients. To allow for 30% dropout a sample size of 350 randomised participants is sought.

As there is uncertainty on both healing rates and dropout rates, the Data Monitoring Committee (DMC) will perform an interim based re-estimation of sample size when 140 randomised patients (70 patients in each group) have completed 20 weeks of follow-up. The sample size re-estimation will be done by comparing 20 weeks’ healing proportions from two groups with Fleiss continuity correction, based on two-sided alpha = 0.04 and beta = 80%, on both the intention-to-treat (ITT) and per-protocol (PP) populations.

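### The sample size section labels 80% power as beta in two places, including the re-estimation rule, and its 350 randomised fall slightly short of 250 evaluable at 30% dropout; the 250 itself reproduces exactly

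*Protocol article*

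**What the plan says.** All the figures are in the Sample size section of the protocol article, except the allocation ratio, which is under Design.

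- Method: "A sample size for comparing two proportions with Fleiss continuity correction".
- Error rates and control healing rate for the original calculation: "based on alpha = 0.05 and beta = 80% and with an outcome rate in the control group of 30" per cent. Sidedness is not given in this sentence.
- Treatment effect: "an improvement of 18 percentage points (i.e. to 48%) in the treatment group".
- Allocation: "Patients will be randomised 1:1 to the intervention or the usual-care arm".
- Result: 250 evaluable.
- Dropout: "To allow for 30% dropout a sample size of 350 randomised participants is sought".
- Interim re-estimation by the Data Monitoring Committee, once 140 randomised patients have 20 weeks of follow-up: the same method, "based on two-sided alpha = 0.04 and beta = 80" per cent.

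**The concern.** Two of the printed figures do not agree with their neighbours.

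First, beta is the probability of missing the assumed effect. A beta of 80% is a power of 20%, which is not compatible with the 250 evaluable patients in the same sentence. The label recurs in the re-estimation sentence. There it is more than background, because it is an input to a rule that the committee is to apply, and no sample size is printed beside it to show what was meant.

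Second, the section says 250 evaluable patients are needed and 30% may drop out, but the randomised number it gives does not leave 250 after a 30% loss.

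The power claim and the re-estimation rule rest on these figures, so a reader should be able to reproduce them as printed.

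**Working it through.** **Inputs.** p1 = 0.30, p2 = 0.48, difference d = 0.18, mean proportion 0.39, 1:1 allocation, Fleiss continuity correction, alpha 0.05 (original) or two-sided 0.04 (re-estimation). Two-sided testing is assumed for the original calculation because it is the version that reproduces the printed number.

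**Formulas**, per arm:

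- n = [z(1−alpha/2) × √(2 × 0.39 × 0.61) + z(power) × √(0.30 × 0.70 + 0.48 × 0.52)]² / d²
- Fleiss: nc = (n/4) × [1 + √(1 + 4/(n × d))]²

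The two square roots are √0.4758 = 0.6898 and √0.4596 = 0.6779.

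**Step 1: reproduce the printed 250.** Alpha 0.05, power 80%:

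- n = (1.960 × 0.6898 + 0.8416 × 0.6779)² / 0.0324 = (1.3519 + 0.5706)² / 0.0324 = 114.1
- nc = 124.9, so 125 per arm and **250 in total**, an exact match.

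Other conventions at 80% power and alpha 0.05 do not match: two-sided without the correction gives 230, one-sided with it 202, one-sided without it 180.

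**Step 2: read beta = 80% literally.** Power is then 20%, and z(power) = −0.8416:

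- n = (1.3519 − 0.5706)² / 0.0324 = 18.8
- nc = 28.9, or about 58 in total.

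**Step 3: the re-estimation rule at the planning rates.** With alpha 0.04, z = 2.054:

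| Reading | n per arm | nc per arm | Total |
|---|---|---|---|
| Power 80% (beta 20%) | 121.9 | 132.8 | 266 (133 per arm) |
| Beta 80% taken literally | 22.1 | 32.2 | about 65 (66 with whole arms of 33) |

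The rule would be run on interim healing proportions, so these totals illustrate it at 30% v 48% and do not predict its result. The literal total is below the 140 patients who must already have completed 20 weeks before the rule is applied.

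**Step 4: the dropout step.**

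- 350 × (1 − 0.30) = 245
- 250 / (1 − 0.30) = 357.1, so 358 randomised (179 per arm)
- Dropout at which 350 leaves 250: 1 − 250/350 = 28.6%
- The other common inflation, 250 × 1.30 = 325, does not give 350 either.

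**Step 5: what 245 costs.** Inverting the Fleiss correction, n = nc × [1 − 1/(nc × d)]². For 245 in total, nc = 122.5 and n = 111.6; then z(power) = (0.18 × √111.6 − 1.3519)/0.6779 = 0.811, a power of 79.1%. For 250 in total, nc = 125 and n = 114.1, giving 80.0%. The loss is 0.9 percentage points.

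**The case against.** The strongest reply is that nothing in the design is wrong. The value 80%, the healing rates, the correction and the 250 all fit together; only the name attached to 80% is wrong, and the 250 in the same sentence settles what it means. The re-estimation rule also cannot sensibly be read literally, since it would then ask for fewer patients than had already been followed. All of this stands. A reader might infer from the printed beta that the trial was planned with 20% power, or that its sample size is unsupported by its own inputs. The document does not support either inference, and the figure of about 58 patients serves only to show that the label cannot be right.

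On dropout, 350 is a recruitment target 2.2% below 358, set against a round planning figure. The section itself acknowledges uncertainty in both healing and dropout rates and provides a re-estimation for that reason. Trial status reports recruitment closed with 269 randomised, so the choice between 350 and 358 no longer governs anything. This also stands, and it limits the dropout point to a minor remark. It does not make the printed step correct: a 30% loss from 350 does not leave 250, and neither usual inflation method returns 350.

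What the reply does not remove is the repetition of the wrong label inside a pre-specified rule. The person applying that rule should not have to correct one of its inputs from context.

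**Conclusion.** The point holds as a correction of stated figures, at low severity. Power is mislabelled as beta in two sentences, one of them the committee's re-estimation rule. The effect on the evaluable sample size is nil: 250 follows exactly from 80% power, two-sided alpha 0.05, 30% v 48% and the Fleiss correction. This rests on one assumption, that the original alpha is two-sided, which the exact match supports.

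The dropout shortfall is real but small: 5 evaluable patients, or 8 randomised, and 0.9 points of power. It is best described as a rounded target whose consequence was not stated. It is not evidence of a materially underpowered design.

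**What to change.** 1. In both sentences of the Sample size section, replace the beta of 80% with power 80% (beta = 20%). Adding that the original alpha is two-sided would make that calculation fully reproducible.
2. Keep 350 and state what it delivers: 245 evaluable and about 79% power at 30% dropout, or 250 evaluable at about 28.6% dropout.

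The cost is wording only. No enrolment, analysis or decision rule changes, apart from the re-estimation input now saying what was intended. The stated power at 30% dropout becomes about one point lower than 80%.

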### Analyses

All analyses will be completed on both the ITT and the PP populations. The primary analysis for outcome will be a logistic regression for the proportions of patients healed within 20 weeks taking into account ulcer area, ulcer depth and ABPI.

All secondary variables will be presented using appropriate descriptive statistics and analysed on the basis of the level of measures and the distribution of scores (where appropriate). Analyses will include survival analysis for time to healing and general linear models for difference in change of pain score; with EQ-5D and SF-12 data presented in line with the conventions for these tools.

Cost-effectiveness and cost-utility analysis will be performed based on the cost-related endpoints collected in the study.

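### The interim re-estimation is driven by the observed treatment difference in 70 patients per arm, and uses an unexplained alpha of 0.04 where the trial was sized at 0.05

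*Protocol article*

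**What the plan says.** All but the last two items are in the Sample size section of the protocol article.

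- **Initial size.** It is "based on alpha = 0.05 and beta = 80" per cent (read as 80% power), with an "outcome rate in the control group of 30% and an improvement of 18 percentage points (i.e. to 48%) in the treatment group". This gives 250 evaluable and 350 randomised patients.
- **Reason for re-estimating.** "As there is uncertainty on both healing rates and dropout rates".
- **Timing.** The DMC acts "when 140 randomised patients (70 patients in each group) have completed 20 weeks of follow-up".
- **Rule.** It compares the 20-week "healing proportions from two groups with Fleiss continuity correction, based on two-sided alpha = 0.04 and beta = 80" per cent, in both the intention-to-treat (ITT) and per-protocol populations.
- **Final analysis (Analyses section).** "The primary analysis for outcome will be a logistic regression for the proportions of patients healed within 20 weeks", adjusted for ulcer area, ulcer depth and ABPI. The article gives no significance level for it.
- **Progress (Trial status section).** 269 participants were randomised and recruitment has closed.

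The article does not say why alpha moves from 0.05 to 0.04.

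**The concern.** The stated reason and the rule do not match. The overall healing proportion and the dropout rate are nuisance quantities, and both can be re-estimated without looking at the arms separately. The rule compares the two arms. What it mainly feeds into the formula is therefore the observed treatment difference, and required size varies roughly with the inverse square of that difference. With 70 patients per arm the difference is poorly estimated, so the new target is too.

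Two things are at stake. The first is power: a step meant to protect it may set a target that is far too small or unattainably large. The second is the meaning of the final p-value. When the size depends on the interim effect and all data are then pooled in a conventional test, the nominal level is not exactly preserved. With two alphas in the text and none in the Analyses section, a final p-value between 0.04 and 0.05 has no agreed interpretation.

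**Working it through.** **Inputs from the article.** p1 = 0.30, p2 = 0.48, d = 0.18, power 80%, 1:1 allocation, 70 per arm at the interim, alpha 0.05 (sidedness not given; two-sided reproduces the stated size) and two-sided alpha 0.04.

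**Formula (Fleiss).** With p̄ = 0.39:

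- n′ = [zα√(2p̄(1−p̄)) + zβ√(p1(1−p1) + p2(1−p2))]² / d²
- n = (n′/4)·[1 + √(1 + 4/(n′d))]²
- √(2 × 0.39 × 0.61) = 0.6898, √(0.21 + 0.2496) = 0.6779 and zβ = 0.8416.

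**Step 1: reproduce the plan's figure (alpha 0.05).** n′ = (1.960 × 0.6898 + 0.8416 × 0.6779)²/0.0324 = 1.9226²/0.0324 = 114.1. The correction gives n = 124.9, so 125 per arm and 250 in total, as stated.

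**Step 2: same inputs at alpha 0.04.** n′ = (2.0537 × 0.6898 + 0.5706)²/0.0324 = 121.9 and n = 132.8, so 133 per arm and 266 in total.

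**Step 3: power of 250 at alpha 0.04.** Inverting the correction, √n′ = √125 − 1/(0.18 × √125) = 11.180 − 0.497 = 10.683. Then zβ = (0.18 × 10.683 − 2.0537 × 0.6898)/0.6779 = 0.747, which is 77.2% power.

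**Step 4: precision of the interim difference.** SE = √(0.21/70 + 0.2496/70) = 0.081. If 18 points is true, 95% of observed differences lie between about 2 and 34 points. The quartiles are 18 ± 0.674 × 8.1, about 12.5 and 23.5 points. With control at 30% and alpha 0.04, these give totals of about 524 and 164.

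**Step 5: distribution of the target.** Both arms were simulated at 30% and 48% with 70 patients each, and the total was recomputed by the rule at alpha 0.04.

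| Re-estimated total | Result |
|---|---|
| Median | about 258 |
| Quartiles | about 156 to 518 |
| At or below 140 | about 20% of trials |
| Above 500 | about 27% of trials |
| Within 200 to 300 | about 20% of trials |

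For contrast, a blinded rule (pooled proportion from the same 140 patients, 18 points held fixed) gives a 10th to 90th percentile range of 236 to 260 at alpha 0.05, or 252 to 276 at 0.04.

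**Step 6: type I error.** Equal healing in both arms (30% or 39%), size reset by the rule, then a pooled two-proportion z-test as a stand-in for the logistic regression. Floors, caps and the handling of a zero or negative difference are assumptions, so ranges are shown.

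| Final two-sided alpha | Total capped at 350 | Looser caps (700 or 2,000) |
|---|---|---|
| 0.05 | about 5.2% to 5.9% | up to about 7% |
| 0.04 | about 4.2% to just under 5% (highest 4.97%) | 4.3% to 4.8% at 700 if a non-positive difference goes to the cap or floor; 5.1% to 5.5% at 700 with a floor of 140 or 250 if the absolute difference is used; up to 6.1% at 2,000 |

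Without re-estimation the same test gives about 5.0% and 4.0%.

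**The case against.** **The final test may be at 0.04, and 0.04 may be there to pay for the interim.** This largely stands. A reader might infer that the false-positive rate is uncontrolled whatever is done. The documents do not support that: at a final 0.04 with the total capped at 350, the error stays below 5%, and with at most 270 patients, close to the 269 randomised, it is about 4.2% to 4.6%. Most excesses over 5% at 0.04 need caps of 700 or more together with use of the absolute difference. But the article does not say that 0.04 is the final level.

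**The rule might mean something else.** That the committee uses observed arm-level proportions is the natural reading of a comparison of two groups, not an explicit statement. If the planned 18 points were held fixed, the spread in Step 5 would not arise, but the change of alpha would still need explaining. That a DMC does the work limits who sees the data; it does not remove the dependence of size on effect.

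**Other stronger readings.** A reader might call the target random. That goes too far: its median, 258, is close to the 266 required, and the spread is the problem. A reader might also think that healing first seen in weeks 17 to 20 is lost at the interim because the 4-week confirmation is incomplete. But completion of 20 weeks is a trigger for the interim, not a data cut for each patient, and patients randomised more than four weeks before the last of the 140 would have passed week 24. Any cap, floor, dropout step or governing population may stand in the full protocol or DMC charter, so their absence from a condensed article is not held against the plan.

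**Conclusion.** The point holds for the rule as printed. Its stated purpose is to deal with uncertain rates, but it ties the target to the interim treatment effect. Even when the planning assumptions are exactly right, half of all targets fall outside about 156 to 518, so the step cannot reliably protect power.

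The two alphas are inconsistent without explanation. If 0.04 is the final level, the initial size is 16 evaluable patients short (266 − 250), or the stated 80% power is about 77%. The shortfall is modest, and re-estimating at 0.04 would itself size the trial for 0.04.

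Type I error inflation depends on the final alpha and on how far the size can grow. It is about 0.2 to 0.9 percentage points at a final 0.05 with a cap of 350, and there is no excess over 5% at a final 0.04 with that cap. These figures assume observed arm proportions in the formula, a conventional pooled final test, and caps and floors that the article does not give.

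**What to change.** **If the two-group step has not been used.** Re-estimate from the blinded pooled ITT healing proportion and the observed dropout, hold the 18-point difference fixed, and keep alpha at 0.05. This matches the stated reason and costs only wording in the protocol and DMC charter.

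**If it has already been run.** This is the practical case if it took place as planned, since recruitment is closed; the article does not report it. Keep the resulting size and choose one of two routes before the final unblinded analysis:

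- test the primary outcome at two-sided 0.04; or
- test at 0.05 with an inverse-normal combination of the first 140 patients and the later patients, with weights fixed independently of the interim result. Weights from the planned 350 would be √(140/350) = 0.632 and √(210/350) = 0.775.

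The combination test loses a little efficiency against a pooled test. Neither route needs extra patients.

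**In either case.** Say what 0.04 was for, state one final alpha in the Analyses section, and use it in both sample-size statements. If it is 0.04, restate the initial requirement as 266 evaluable patients, or the power at 250 as about 77%.
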